**Figure 1 clc23254-fig-0001:**
[figure not shown]
Study flow chart. ACS, acute coronary syndrome; BAQ, Brilique Adherence Questionnaire; GRACE, Global Registry of Acute Coronary Events; LSQ, Lifestyle Changes Questionnaire; MEMS, medication event monitoring system; NSTEMI, non‐ST segment elevation myocardial infarction; SF‐36, 36‐item Short‐Form Health Survey; STEMI, ST‐elevation myocardial infarction; UA, unstable angina pectoris

### Endpoints

2.2

The primary outcome variable is the percentage of tablets that patients report to have taken during the 48‐week observation phase, measured by the BAQ. The main secondary outcome variables include the percentage of tablets taken during the 48‐week observation phase, using the information from MEMS. Furthermore, the percentage changes from baseline to the second visit to determine key risk factors (including blood pressure and laboratory parameters), in quality of life (SF‐36v2, see Table A1) and in patient‐reported lifestyle changes (LSQ‐V1 and LSQ‐V2, see Table A1) were studied. Understanding of the disease and treatment awareness as assessed by the BAQ questions 5 to 11, health‐care utilization based on BAQ questions 12 to 15 and cardiovascular risk score (GRACE 2.0, see Table A1) complemented the secondary endpoints.^25^

### Statistics and study analysis

2.3

The Student's *t* test assuming equal variances was used for the sample size calculations based on μ = percentage of tablets the patient reported to have taken. The test hypothesis was H_0_: μ_active_ = μ_control_ and H_A_: μ_active_ − μ_control_ ≥ 0.07 with a two‐sided α of 0.05 and a power of 85%. In other words, we test the hypothesis that the adherence rate is at least 7% higher in the smartphone‐supported patient group with a power of 85%.

Based on these assumptions, we calculated the 231 patients per arm. A 1‐year study of 243 randomized patients reported an approximately 5% drop out rate.^11^ However, a worst‐case dropout rate of 30% was assumed given the uncertainty of this novel approach, the setting of clinical practice within a observational framework, the potential technology barrier in the target population, and uncertainties of patient reporting in this study. The resulting final sample size was therefore estimated with 340 patients per arm with a total of 680 patients.

There are no substudies planned in the original protocol (http://clinicaltrials.gov Identifier: NCT02615704). However, post‐hoc analyses may be indicated depending on the findings of the planned study results within the framework of the a priori defined statistical analysis plan. Post‐hoc power calculations are planned for key secondary endpoints such as the percentage of tablets taken during the 48‐week observation phase and the percentage changes from baseline to the second visit in terms of key risk factors.

### Study organization

2.4

This study was performed in compliance with Good Clinical Practice, including the archiving of essential documents. Data management, randomization, and statistical analysis were done by an independent third party. The study involved a steering committee consisting of five principal investigators as listed in Table B1.

## PRELIMINARY RESULTS

3

Preliminary results are available in Table 3. As published at http://clinicaltrials.gov, the study was started in February 2016, whereas the actual primary completion date was reached in March 2019. The data validation and finalization as well as the analyses are ongoing until October 2019.

**Table 3 clc23254-tbl-0003:** Preliminary demographic data

Variable	All patients	Active group	Control group
Number of patients	664	332	332
ACS			
Unstable angina pectoris	91 (13.7%)	47 (14.2%)	44 (13.3%)
NSTEMI	331 (49.9%)	165 (49.7%	166 (50.0%)
STEMI	242 (36.4%)	120 (36.1%)	122 (36.7%)
Age (years) mean +/− SD	56.3 ± 9.5	56.6 ± 9.1	56.0 ± 9.9
Male gender	573 (86.3%)	284 (85.5%)	289 (87.0%)
Diabetes	117 (17.6%)	62 (18.7%)	55 (16.6%)
Hypertension	463 (69.7%)	235 (70.8%)	228 (68.7%)
Prior PCI	390 (58.7%)	199 (60.0%)	191 (57.5%)
Hyperlipidemia	380 (57.2%)	192 (57.8%)	188 (56.6%)
Obesity	178 (26.8%)	82 (24.7%)	96 (28.9%)
Medication			
Statin	564 (84.9%)	282 (84.9%)	282 (84.9%)
Beta‐blockers	528 (79.5%)	272 (81.9%)	256 (77.1%)
ACE inhibitor	435 (65.5%	219 (66.0%)	216 (65.1%)
Angiotensin receptor blockers	126 (20.0%)	66 (19.9%)	60 (18.1%)
Diuretics	89 (13.4%)	46 (13.9%)	43 (13.0%)
Calcium channel blocker	83 (12.5%)	43 (13.0%)	40 (12.0%)

## DISCUSSION

4

Non‐adherence to comedication and lifestyle advice has a marked impact on therapy success and patients' outcomes. Adherence rates as low as 40% to 50% for long‐term treatment are typically reported in the literature whereas the impact is often underestimated in clinical practice and health‐cost estimates.^1^, ^26^, ^27^, ^28^, ^29^ There are various reasons for non‐adherence and not all reasons can be influenced by support tools or strategies. The primary objective of the eMocial trial is to evaluate the effect of patient support through a smartphone‐based app on treatment adherence. Our target group are patients with ACS who follow a DAPT regimen according to the most recent ESC guidelines.

### Adherence tools

4.1

Consideration was given to different methods of tracking adherence when designing this study. A broad range of direct and indirect methods to characterize adherence are available but there are some challenges to accurately measure therapy adherence. The act of measuring patients' adherence is likely to have an impact on adherence activity. In addition, one can expect a potential motivational impact.

The more the measurement methodology influences patients' daily routines, the higher will be the adherence to treatment. It is therefore important to balance the requirement for highly granular, objective data with the need to interfere as little as possible with the results.

Objective and passive measures that collect data without the patient thinking about it would be the most desirable.

The MEMS device used in this study is also known as the “Helping Hand.” This device holds a medication blister, inserted by the patient, and registers the date and time whenever the medication is taken out from the package. Although originally designed as a tool to help improve adherence, it was adjusted so that it does not remind patients or visualize anything on the device. Data from a long‐term study have shown that the impact on adherence is only short term (less than 30 days),^30^ so the impact on a 12‐month study can be considered as small.

The use of PRO tools to capture adherence is common, but there are two major challenges with this approach. The first concern is data bias due to, for example, variable patient recall and social desirability (ie, patients feeling an expectation about how to answer questions). Because we are asking patients to report on something they are supposed to be actively doing (rather than something they experience or perceive), self‐reports on adherence tend to overestimate adherence. The second concern is the validity of current instruments. To our knowledge, there are no currently available adherence tools that would meet regulatory standards of being “fit for purpose” in terms of content and psychometric characteristics.^22^, ^23^ Thus, we designed our own instrument to measure both intentional and unintentional adherence for use in the eMocial study, the BAQ.

The advantage of using a smartphone‐based app (Appendix C) to judge therapy adherence in clinical practice is that actual clinic visits are not required. Furthermore, there are no clinical follow‐ups outside the standard of care during the 12‐month period and no follow‐ups if patients do not complete the surveys after initial enrolment in the study. Thus, the patients will only follow standard of care in the real‐life setting and improvements in adherence will be likely to stem from the benefits of using the smartphone‐based patient support tool app. Based on the same rationale, no prescribed treatment drug is provided in this study.

### Limitations

4.2

One limitation of this study is the lack of closely comparable statistical data for study dropout and response rates to PRO tools delivered through the patients' own mobile devices. This means that the assumptions made for the sample size calculations are approximate. Consequently, there is a risk of not being able to establish statistical significance. In addition, because study‐specific health‐care professional interactions are minimized, there is a risk that patients in the study could stop responding to the PRO surveys even if they continue medication.

In terms of the postulated rather conservative dropout rate of 30%, as compared to the reference values discussed by Akl et al,^31^ we would like to propose a comparison of all patient demographics and risk factors in the patient group with and without follow‐up. If these comparisons do not reveal a higher risk profile for those patients who were lost to follow‐up, one could reasonably assume that difficult‐to‐treat patients are not excluded to present better outcomes.

In this study, the accuracy and granularity of adherence measurement are balanced with the risk of affecting the adherence by the act of measuring it. This is done by presenting BAQ every 4 weeks (ie, seldom enough to have a low effect on adherence) and then asking the patients for their number of missed doses in the past 7 days (ie, a short enough recall period for the patient to be able to remember). The weekly non‐adherence rate is then extrapolated to the full 4‐week period since the previous measurement. The fact that the PRO tools are new and not yet fully validated is also a limitation of this study. Because 50% of the study population use MEMS, cross‐correlation between the PRO and MEMS adherence numbers will be possible.

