### Investigational app

1.4

A medical, smartphone‐based app, “Me & My Heart”, has been developed to increase treatment adherence (medication and lifestyle changes) by combining reminders about medication intake, information on the importance of treatment, motivation by supportive messages, and visualization of the effect of an individual's lifestyle choices on cardiovascular risk (specifically for patients with ACS who are prescribed drugs such as ticagrelor). The app is CE (Conformité Européene) marked as a class I medical device. The patient enters baseline information and the tool will then allow the patient to enter data on an ongoing basis and provide individualized feedback to the patient. The app will send daily optional reminders for medication intake, as well as motivational and informative messages every couple of days. The relationship between cardiovascular risks and lifestyle choices is graphically displayed in a qualitative way on a continuous basis.

In addition, the “Me & My Heart” app delivers monthly questionnaires to evaluate the trial endpoints. For the control group, the app will deliver only the questionnaires to evaluate endpoints and will not give any of the previously mentioned patient support. To assess if this information has an effect on the patients' lifestyle, we included an in‐house developed instrument, the Lifestyle Changes Questionnaire (LSQ; Appendix B1), which asks patients about diet, exercise and smoking habits. The 36‐item Short‐Form Health Survey was also included to understand the possible impact on health‐related quality of life (QOL).

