- e‐diary with option to set targets for exercise, body weight, and smoking. Personalized motivational messages were also used to promote life style changes (exercise level, body weight reduction, smoking cessation/reduction).
- A treatment index based on the patients' total activities to align with established treatment guideline (adhere to oral antiplatelet treatment, reduction in body weight if BMI > 25, smoking cessation and moderate exercise >150 minutes per week according to WHO recommendation). Individuals' development per week as well as comparison with the other patients' performance was given to recognize good work or stimulate further work if needed
- A screenshot for exercise summary is shown below:

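### The one comparison of self-report with MEMS that the article names is a correlation, which is essentially blind to over-reporting that is larger in the active arm; a by-arm BAQ-minus-MEMS difference on the same data would show it

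*Protocol article*

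**What the plan says.** Section 2.2 defines the primary outcome as the percentage of tablets patients report having taken over 48 weeks, measured by the BAQ. The BAQ asks every 4 weeks about the past 7 days, and the weekly non-adherence "rate is then extrapolated to the full" 4 weeks (section 4.2).

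Section 4.1 names recall and social desirability as sources of bias and says that self-reports "on adherence tend to overestimate adherence". It treats this as a general tendency and does not discuss whether it could differ between arms. It goes on to say that improvements in adherence would probably come from the support tool.

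The arms differ in what surrounds the questionnaire. Section 1.4 says: "For the control group, the app will deliver only the questionnaires to evaluate endpoints". The active app adds reminders, information on why treatment matters and motivational messages. The appendix list of app features adds a treatment index that includes antiplatelet adherence; feedback on the patient's own progress and comparison with other patients' "performance was given to recognize good work or stimulate further work if needed".

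Section 4.2 acknowledges that the questionnaires are new and not fully validated. It then says that cross-correlation "between the PRO and MEMS adherence numbers will be possible", because half the patients use MEMS.

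MEMS has a second role. Section 2.1 randomises each arm 1:1 to MEMS or no MEMS. Table 1 makes the app's effect on MEMS-recorded tablets taken a secondary objective, and section 2.2 lists that measure first among the main secondary outcomes.

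**The concern.** The questionnaire reaches both arms through the app, but only active patients are coached on adherence and shown how they compare with others. That could raise tablet-taking. It could also raise the wish to report good tablet-taking, and the primary comparison would count both as benefit.

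A correlation between BAQ and MEMS asks whether patients who score higher on one also score higher on the other. It does not ask whether BAQ sits above MEMS, or further above it in one arm. A high correlation could therefore be taken as reassurance about a bias that it does not measure. Nor does it test whether the recalled week represents the three weeks to which it is extrapolated, which again could differ by arm.

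At stake is how a positive primary result is worded: as better adherence, or as better reported adherence.

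**Working it through.** **Inputs from the article.** Section 2.3: a Student's t "test assuming equal variances was used for the sample size calculations"; two-"sided α of 0.05 and a power of 85"%; the hypothesis that "the adherence rate is at least 7% higher in the smartphone" group, i.e. 0.07; 231 evaluable per arm; 30% dropout; 340 randomised per arm. Table 3: 332 per arm. Section 2.1: MEMS in half of each arm. The article gives no SD.

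**1. The plan's own figure.** The SD implied by 231 per arm is 0.07 × √(231/2) / (1.960 + 1.036) = 0.251. With SD 0.25 the t test needs 230.005, so 231 per arm. Inflating for dropout, 231/0.70 = 330, against 340 stated (a 2.9% gap). SD 0.25 is therefore used below as an assumption consistent with the plan.

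**2. What correlation does under differential over-reporting.** Suppose there is no true effect and every active patient over-reports by 7 points more than controls.
- Within each arm, adding a constant leaves Pearson's r unchanged. In simulation it stayed at 0.50, 0.70 and 0.90.
- Pooled over arms, the BAQ variance grows by 0.07²/4 = 0.001225, from 0.0625 to 0.063725. So r is multiplied by √(0.0625/0.063725) = 0.990. The values 0.50, 0.70 and 0.90 become 0.495, 0.693 and 0.891; simulation agreed to within 0.001.
- The BAQ arm difference is 0.07, the full design effect.

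The uniform shift is an illustration. Seven points of 14 weekly tablets is 0.98, about one tablet a week, and a patient already at 14 of 14 cannot over-report.

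**3. What the planned MEMS arm comparison can do.** MEMS patients per arm: 340/2 = 170, or 170 × 0.70 = 119 after 30% loss. Power for a true 7-point difference (two-sample t test, 0.05 two-sided):

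| Assumed SD | 170 per arm | 119 per arm |
|---|---|---|
| 0.20 | 90% | 77% |
| 0.25 | 73% | 58% |
| 0.30 | 57% | 43% |

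At SD 0.25 and 119 per arm, the 95% CI half-width is 1.96 × 0.25 × √(2/119) = 6.4 points. A real 7-point effect would miss significance on MEMS about 42% of the time. A non-significant MEMS result beside a positive BAQ result would therefore be hard to read on significance alone.

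**4. What a direct BAQ-minus-MEMS contrast can do.** From Table 3, 332/2 × 0.70 gives about 116 per arm. The half-width of the between-arm difference is 1.96 × SD of the discrepancy × √(2/116) = 0.257 × SD:
- SD 0.10: 2.6 points
- SD 0.15: 3.9 points
- SD 0.25: 6.4 points

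With no loss (166 per arm) these become 2.2, 3.2 and 5.4 points.

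If both measures have SD 0.25, the discrepancy SD is 0.25 × √(2(1 − r)). The three SDs then correspond to r of about 0.92, 0.82 and 0.50. Power to detect a 7-point difference in over-reporting with 119 per arm is 44%, 58%, 79% and above 99% at r = 0.3, 0.5, 0.7 and 0.9. At r = 0.3 the half-width is about 7.5 points, so precision depends on how well the measures agree.

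**The case against.** A reader might infer that the correlation is the trial's sole safeguard, and that a positive primary result could never be told apart from flattering self-report. The documents do not support that. MEMS is randomised within both arms, and its arm comparison is the first-listed main secondary outcome. In the scenario above it would be expected near zero while BAQ showed 7 points. Among patients with both measures over the same periods, the arm difference in BAQ minus MEMS is simply the BAQ arm difference minus the MEMS arm difference. The requested analysis adds matched windows and a paired confidence interval, not new information.

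A reader might also infer that the active app ranks patients. The appendix describes only a comparison with others' performance.

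Three further points have weight. Section 4.2 says only that cross-correlation is possible, in a remark on instrument validation; it fixes no coefficient or decision rule. An analysis plan is mentioned but not shown, and it may contain an agreement analysis, so its absence from the article is not the complaint. The ceiling at 14 tablets means a uniform shift is not generally attainable, so exact invariance of the correlation is an idealisation.

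What remains is that the comparison the article chose to name is poorly suited to the bias that its own design makes plausible. Nothing in the article says that the primary result will be read together with the MEMS contrast.

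**Conclusion.** The point holds as a low-cost improvement and is not a flaw that invalidates the primary analysis. Cross-correlation is essentially insensitive to over-reporting that is larger in the active arm, and the article does not consider that possibility. In the idealised case, a reporting shift equal to the whole 7-point design effect moves the pooled correlation by less than 0.01.

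The planned MEMS comparison is a real safeguard, but a weak one: about 58% power for 7 points with 119 per arm (43% to 77% over SD 0.30 to 0.20), against 85% planned for the primary endpoint. It is also not linked to the interpretation of that endpoint.

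These sizes rest on assumed SDs and correlations, on 30% loss, and on normal theory for a bounded measure that is probably skewed. MEMS records removal from the blister and not ingestion, so it is a better reference than self-report but not a perfect one.

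**What to change.** In the MEMS half of each arm, replace or supplement the cross-correlation with an agreement analysis fixed before the arm comparison is seen:

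1. Compute each patient's BAQ-minus-MEMS difference over matched 7-day windows. Summarise it by arm (Bland-Altman bias and limits), and give the between-arm difference with its 95% CI.
2. Compare MEMS adherence in recall weeks with the other three weeks, by arm, to test the extrapolation.
3. Report the MEMS arm difference beside the primary BAQ result, and state that a BAQ effect will be read as true adherence only in that light.

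If the analysis plan already contains these steps, a sentence in section 4.2 in place of the cross-correlation remark is enough. No new data are needed. The cost is a little extra analysis and possibly a more cautious primary claim.

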## CONCLUSIONS

5

This study will evaluate how a mHealth solution can support ACS patients and positively impact their adherence to both medication and lifestyle changes over a clinically relevant treatment time of 12 months. If conclusive, our study could significantly help to understand how inadequate adherence to comedication could be improved with a smartphone‐based application.

## APPENDIX A 1

**Table A1 clc23254-tbl-0004:** Other scores for secondary endpoints

SF‐36v2®	The SF‐36 consists of eight scaled scores, which are the weighted sums of the questions in their section. Each scale is directly transformed into a 0‐100 scale assuming that each question carries equal weight. The lower the score the higher is the degree of disability. The higher the score the less disability, that is, a score of zero is equivalent to maximum disability and a score of 100 corresponds to no disability. The eight sections are: vitality, physical functioning, bodily pain, general health perceptions, physical role functioning, emotional role functioning, social role functioning, and mental health.^32^
LSQ‐V1 and LSQ‐V2	Evaluation of lifestyle changes by Lifestyle Changes Questionnaire (LSQ)‐V1 and ‐V2 (patient‐reported outcome [PRO] instrument, developed for this trial). Questions with regard to a healthy diet, smoking behavior or regular exercise at the beginning (V1) and end (V2) of the trial to evaluate lifestyle modifications.
GRACE 2.0	GRACE is a risk score for ACS patients^25^ Inputs to calculate the mortality risk based on the GRACE score, which can range between 1 and 210. Inputs are age, heart rate, systolic blood pressure, amnestic presence of heart failure, prior MI, ST elevation, serum creatinine concentration, increased myocardial enzymes, and conducted coronary intervention

## APPENDIX B 1

**Table B1 clc23254-tbl-0005:** Study centers

No.	Study center	City	Principal investigator
01	Kliniken Maria Hilf	Mönchengladbach	[name]. [name]
02	Herzzentrum Wuppertal	Wuppertal	[name] [name]
03	Klinikum der Universität Regensburg	Regensburg	[name]. [name]
04	Asklepios Klinik St. Georg	Hamburg	[name]
05	Zentralklinik Bad Berka	Bad Berka	[name]‐[name]
06	Herz u. Kreislaufzentrum Rotenburg a.d. Fulda	Rotenburg a.d. Fulda	[name]
07	Ambulantes Herzzentrum Kassel	Kassel	[name]‐[name]
08	Charité—Campus Virchow‐Klinikum	Berlin	PD [name] (coordinating investigator)
09	Klinikum Coburg	Coburg	[name]. [name]

- e‐diary with option to set targets for exercise, body weight, and smoking. Personalized motivational messages were also used to promote life style changes (exercise level, body weight reduction, smoking cessation/reduction).
- A treatment index based on the patients' total activities to align with established treatment guideline (adhere to oral antiplatelet treatment, reduction in body weight if BMI > 25, smoking cessation and moderate exercise >150 minutes per week according to WHO recommendation). Individuals' development per week as well as comparison with the other patients' performance was given to recognize good work or stimulate further work if needed
- A screenshot for exercise summary is shown below:
